### Data Management

Personal and identifiable data will be collected from patients. Data will be kept confidential and managed in accordance with the Data Protection Act, General Data Protection Regulation policies and Swedish Act concerning the Ethical Review of Research Involving Humans (SFS 2003:460). Data will be held on services located within the Region Skåne databases, stored and secured both physically (in locked cabinets designed for the purpose) and electronically (behind firewalls), and be accessible to the study team only.

### Statistical Analysis

Preliminary analyses will be conducted with regression analyses, paired sample *t* tests and ANOVAs. Analyses of pre- to postintervention change will be based on probability modeling using both unadjusted and adjusted models with 95% CIs. Appropriate interaction terms will be included to test subgroup differences in the models [29]. Analyses will be performed in Mplus [30].

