### Randomization

Participants will be randomized in a 1:1 ratio to either intervention or control. The study will include a total of 160 participants, applying a random allocation sequence using the “chit method” by preparing 160 chits of paper indicating either control or treatment [21]. Each patient will be allocated to a condition (control or treatment), and the chit will not be replaced if the patient drops out of the study. The allocation to treatment and control arms may thus be uneven at certain times during the trial, but the end result of randomization will result in an equal distribution between control and treatment. It will not be possible to blind participants, clinicians, or supervising researchers to randomization allocation. The control group will receive “treatment as usual” at their home clinic. For an overview of recruitment and randomization, see the flow diagram in Figure 1.

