### Sample Size

Patients who have agreed to participate in the treatment study will be randomized in a 1: 1 ratio between intervention and control group. In our power calculation, we estimated that 40% in the intervention group and 20% in the control group will see improvement through the treatment offered in different groups, and after this treatment fall under the cutoff for problem gaming. With these figures, 160 (80 + 80) patients must be included in the treatment study for us to be able to demonstrate a significant difference with sufficient power. Given the large number of patients in pediatric and youth psychiatry in the region and the likely high incidence of problem behaviors in the population, we believe it is possible to reach this number of participants in the study.

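### Statistical Analysis describes pre-to-post change and does not state the between-arm comparison of proportions under the gaming cutoff on which the 160 participants are based

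*Protocol article*

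**What the plan says.** Sample Size in the protocol article rests on a randomised contrast of a binary outcome: "we estimated that 40% in the intervention group and 20% in the control group will see improvement", where improvement means that patients "after this treatment fall under the cutoff for problem gaming". From this it concludes that "160 (80 + 80) patients must be included in the treatment study" in order "to demonstrate a significant difference with sufficient power". Randomization sets the contrast up: "Participants will be randomized in a 1:1 ratio to either intervention or control". The second specific objective under Aim and Objectives is to establish effectiveness by means of the randomised trial.

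Statistical Analysis reads differently. It opens with "Preliminary analyses will be conducted with regression analyses, paired sample" t tests and ANOVAs. The next sentence is: "Analyses of pre- to postintervention change will be based on probability modeling using both unadjusted and adjusted models with 95% CIs". Interaction terms are mentioned only for differences between subgroups. The section names no arm, cutoff, proportion or treatment contrast. The Abstract has the same slant, describing the primary outcomes as gaming and gambling measures taken before and after the intervention.

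**The concern.** The sample size and the analysis section describe different quantities. One is a difference between randomised arms in a proportion at the post rating. The other is change from before to after. Followed literally, the analysis section contains no test of what the trial was sized to detect.

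The gap is not harmless in this population. Under Recruitment and Eligibility, children are screened at their first visit and enter because they meet problem-gaming criteria. A group chosen for high scores tends to score lower when rated again, through regression to the mean, natural course and usual care. A within-arm comparison counts all of that as improvement. If such a comparison were read as evidence of efficacy, relapse prevention would look effective whether or not it is. Participants, clinicians and supervising researchers all know the allocation, so the deciding comparison should be fixed in writing.

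**Working it through.** **1. Reproducing the 160.** Inputs from Sample Size: 0.40 and 0.20, 80 per arm, 1:1. Alpha and a numerical power are not given. I assume two-sided 5%, consistent with the 95% CIs in Statistical Analysis, and 80% power.

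Pooled formula: n per arm = [z(0.975)·√(2·p̄·(1−p̄)) + z(0.80)·√(p1(1−p1) + p2(1−p2))]² / (p1−p2)², with p̄ = 0.30.

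- First term: 1.96 × √0.42 = 1.270
- Second term: 0.842 × √(0.24 + 0.16) = 0.532
- n = (1.270 + 0.532)² / 0.04 ≈ 81.2, so 82 per arm or 164 in total

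The unpooled formula gives 78.5 per arm and the arcsine formula 80.3. At 80 per arm the pooled formula gives 79.4% power. Exact enumeration gives 80.1% for the uncorrected chi-square test and 74.5% for Fisher's exact test. The 160 is therefore a two-arm comparison of proportions at about 80% power.

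**2. A within-arm test on the protocol's own control rate.** Suppose relapse prevention adds nothing, so 20% fall under the cutoff in each arm: 0.20 × 80 = 16 children per arm. Assume every child starts at or above the cutoff, as the entry criterion implies. Then crossings can only go downward, and the exact McNemar p-value for d crossings is 2 × 0.5^d.

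| Children crossing, of 80 | Exact p |
|---|---|
| 5 | 0.0625 |
| 6 | 0.031 |
| 16 | 0.00003 |

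With a true rate of 20%, the chance of at least 6 crossings in 80 is 99.9%. Either arm, taken alone, would almost certainly show significant improvement.

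**3. The same check for paired t tests.** This needs assumptions beyond the protocol: bivariate normal scores, no treatment effect, test-retest correlation 0.5 to 0.9, and entry restricted to the top 6.7% or the top 20%. The 6.7% is 5.1% + 1.6% from the European survey in Background. The 20% is an assumption. There were 80 children per arm and 1,000 simulated trials per setting.

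| Result with no treatment effect | Range over settings |
|---|---|
| Mean change | −0.14 to −0.97 SD |
| Children below the cutoff at retest | 25% to 73% |
| Within-arm paired t test significant | 81% to 100% |
| Between-arm t test on change significant | 3.7% to 6.3% |
| Between-arm test of proportions significant | 4.2% to 5.6% |

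Both between-arm tests stay near the nominal 5%. The within-arm test does not.

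**The case against.** The strongest reply is that Statistical Analysis leaves the contrast open and does not exclude it. A reader might infer that the trial will judge efficacy by paired t tests. The text does not support that: those tests and the ANOVAs are labelled preliminary, and the sentence on change assigns it to unspecified probability modelling. That could be a logistic model of falling under the cutoff with an arm term. Regression and ANOVA can also compare arms, and a randomised trial of effectiveness implies such a comparison. This stands, and it limits the point to what the section fails to state.

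It is also fair that regression to the mean does harm only if within-arm change supports the efficacy claim. Step 3 shows that comparing change between arms rated at the same interval is not distorted by it.

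A third reply is that covariates, the handling of missing ratings and the ranking of unadjusted and adjusted models usually belong in an analysis plan, which is not shown. This also stands. A reader might infer that reporting both models lets the result be picked afterwards, but an unseen plan may settle that. What remains is that the article itself describes an analysis that differs from the basis of its sample size.

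Finally, a reader might infer a large loss of precision from analysing change scores. With equal variances and r = 0.3 the factors are 2(1−r) = 1.40 and 1−r² = 0.91. Selection at entry removes that equality. With the top 6.7% selected, baseline variance is about 0.15. At a retest correlation of 0.6 the change-score variance is 0.4² × 0.15 + 0.64 ≈ 0.66, against 0.64 after baseline adjustment. The gain is 3.6%, falling to 1.6% at a correlation of 0.8. Precision is not the argument here.

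**Conclusion.** The point holds as a mismatch between two sections. Sample Size depends on a between-arm difference in the proportion under the cutoff. Statistical Analysis describes pre-to-post change and never states that difference. On the protocol's own 20% control rate, a within-arm test is close to certain to be significant with no effect of relapse prevention (16 of 80, p = 0.00003), so it cannot serve the effectiveness objective.

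The McNemar figure assumes that every randomised child starts at or above the gaming cutoff. Intervention also mentions patients who qualify through gambling, and any such child below the gaming cutoff would weaken it slightly. The simulation rests on assumed retest correlations and selection fractions. The power of about 79% to 80% assumes two-sided 5% and a post rating for all 160. The documents do not show that a within-arm test will be the deciding one.

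**What to change.** In Statistical Analysis, name one primary analysis: the intervention-versus-control difference in the proportion under the problem-gaming cutoff at the post rating, in all randomised children. Logistic regression with an arm term, adjusted for the baseline Game Addiction Scale for Adolescents score already collected, would do this. State that the unadjusted model is a sensitivity analysis and that paired t tests only describe change within each arm. The primary outcome should stay the proportion: making the continuous scale score primary would leave the mismatch with Sample Size in place.

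The post rating needs one definition for both arms. Measures and Data Collection rates the intervention arm after treatment, which Intervention puts at 7 to 9 weeks, and the control arm 3 months after inclusion. These sections must be reconciled, since otherwise even the between-arm comparison mixes arm with time since baseline.

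The analysis change costs a sentence or two, uses only ratings already planned and leaves N at 160.

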### Recruitment and Eligibility

The trial and the recruitment will be carried out in several outpatient child and youth psychiatric clinics in Region Skåne in southern Sweden. As part of routine practice, all children (ages 12-18 years) coming for their first visit to 4 child and youth psychiatric units in Region Skåne will be screened for gaming or gambling behaviors. Children will be eligible to be included in the trial if they are aged 12-18 years and referred to outpatient child and youth psychiatric clinics in Region Skåne, meet criteria for problem gaming and internet gaming disorder, and have capacity to provide written informed consent. Children below the age of 15 years need to have their caregivers’ consent. Children will be excluded if they do not speak Swedish. The clinicians who meet children during their first visit to the child and youth psychiatric unit will inform and invite the eligible children to participate in the study.

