The treatment consists of three parts: (1) setting goals, (2) understanding and identifying high-risk situations and problem behaviors, and (3) consolidating the new activity schedule and identifying future high-risk behaviors. The first part is focused on examining the patient’s undesirable behavior, his/her motivation for change, and establishing goals with the treatment (this part primarily draws on motivational interviewing). This part of the treatment therefore varies between 1 to 3 sessions as participants may have different levels of motivation for changing their primary problem behavior, which is why some participants may require 1 or 2 extra sessions at the start of the treatment. The second part (drawing more from traditional CBT techniques) consists of exploring problematic situations using functional analysis; identifying high-risk situations and events, emotions, and cognitions that induce the problematic gaming behavior or result in a relapse; and managing game time with activity scheduling and practicing problem-solving skills. The final part consists of recognizing early warning signals that may indicate that the primary problem behavior is more likely to occur and consolidating the parts of the treatment that have been the most helpful in maintaining the new activity schedule.

Clinicians (psychiatrists and psychologists) with training in CBT will beforehand be educated in relapse prevention and will throughout the treatment be supervised by a clinician with vast experience of treating adults with gambling and gaming addictions.

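### Relapse prevention is given by specially trained clinicians in one arm only, but no named analysis accounts for clinician and the sample size allows nothing for clustering

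*Protocol article*

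**What the plan says.** Allocation is by child: "Participants will be randomized in a 1:1 ratio to either intervention or control" (Protocol article, Randomization). The control arm receives usual treatment at the home clinic.

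On delivery, the Intervention section says that "Clinicians (psychiatrists and psychologists) with training in CBT will beforehand be educated in relapse prevention". These clinicians are supervised throughout, and they treat each child individually. The number of clinicians and the number of children each will treat are not given.

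The Statistical Analysis section lists regression, paired t tests and ANOVAs as preliminary analyses. For the main question it says that "Analyses of pre- to postintervention change will be based on probability modeling using both unadjusted and adjusted models with 95% CIs". It mentions interaction terms for subgroups and names the software. It does not mention clinician, clinic or any form of clustering.

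The Sample Size section says that "we estimated that 40% in the intervention group and 20% in the control group will see improvement", and concludes that "160 (80 + 80) patients must be included in the treatment study" in order "to demonstrate a significant difference with sufficient power". It states no power, no significance level and no inflation for clustering.

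**The concern.** In an individually randomised trial of a talking therapy, the clinician is part of the treatment. If some clinicians get better results than others, children treated by the same clinician resemble one another, and the relapse prevention arm carries less information than 80 independent children would. A newly taught therapy confined to one arm is the usual setting for a partially nested design, with clustering by provider in that arm and possibly little or none in the other.

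If a model with independent errors is fitted to such data, the variance of the treated arm's mean is understated. The CI for the arm difference then covers the true value less than 95% of the time, and differences between individual clinicians can be taken for an effect of the therapy. A test that handles the clustering correctly keeps its error rate but has less power than planned.

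**Working it through.** **Inputs from the article.** Response 40% with relapse prevention and 20% in control; 80 per arm (Sample Size). Individual 1:1 allocation (Randomization). 95% CIs (Statistical Analysis).

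**Assumed, because not given.** Two-sided 5%, in line with the 95% CIs; 80% power; k = 4 to 40 relapse prevention clinicians with equal caseloads m = 80/k; clinician ICC 0.01 to 0.10; clustering in the relapse prevention arm only.

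**Step 1: reproduce the stated sample size.** With pooled variance under the null hypothesis and p̄ = 0.30:

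n per arm = [1.96·√(2·0.30·0.70) + 0.842·√(0.24 + 0.16)]² / 0.20² = (1.270 + 0.532)² / 0.04 ≈ 81.2, so 82 per arm and 164 in total.

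The unpooled formula gives 79 per arm and the arcsine formula 81. Power with 80 per arm is Φ[(0.20 − 1.96·√(0.42/80)) / √(0.40/80)] = Φ[(0.20 − 0.1420)/0.0707] = Φ(0.82) = 79.4%. The stated 160 is therefore an ordinary calculation for independent children. Two-sided variants with a continuity correction (182) or 90% power (218) do not match. A one-sided test at 80% power needs only 128, which would leave room for an inflation, but the article mentions neither a one-sided test nor an inflation.

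**Step 2: add clinician clustering to one arm.**

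- Design effect: DE = 1 + (m − 1)·ICC, applied to the relapse prevention arm.
- Ratio of true to naive SE: r = √[(0.24·DE + 0.16)/0.40].
- Coverage of the naive 95% CI: 2·Φ(1.96/r) − 1.
- Power of a test that allows for the clustering: Φ{[0.20 − 1.96·√(0.21·(DE + 1)/80)] / (0.0707·r)}.

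Example with 8 clinicians and ICC 0.10: m = 10, DE = 1.90, r = √[(0.456 + 0.16)/0.40] = √1.54 = 1.241. Coverage is 2·Φ(1.579) − 1 = 88.6%. Power is Φ[(0.20 − 0.1710)/0.0878] = 62.9%.

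| Clinicians | m | ICC | DE | SE ratio | Coverage | Power | n per arm for 80% power, m held fixed |
|---|---|---|---|---|---|---|---|
| 40 | 2 | 0.01 | 1.01 | 1.003 | 94.9% | 79.2% | 82 |
| 40 | 2 | 0.10 | 1.10 | 1.030 | 94.3% | 77.3% | 86 |
| 16 | 5 | 0.01 | 1.04 | 1.012 | 94.7% | 78.5% | 83 |
| 16 | 5 | 0.10 | 1.40 | 1.114 | 92.2% | 71.4% | 99 |
| 8 | 10 | 0.01 | 1.09 | 1.027 | 94.4% | 77.5% | 86 |
| 8 | 10 | 0.05 | 1.45 | 1.127 | 91.8% | 70.4% | 101 |
| 8 | 10 | 0.10 | 1.90 | 1.241 | 88.6% | 62.9% | 120 |
| 4 | 20 | 0.01 | 1.19 | 1.055 | 93.7% | 75.4% | 90 |
| 4 | 20 | 0.10 | 2.90 | 1.463 | 82.0% | 50.7% | 163 |

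With ICC = 0 the ratio is 1 and coverage is 95% in every row.

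The ratio states how much larger the true SE is than the naive one. The shortfall of the naive SE is 1 − 1/r: at r = 1.241 it is 19% too small, not 24%. All figures use normal quantiles; with few clinicians a small-sample correction would lower the power of a valid test further.

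**The case against.** The strongest reply is that the article does not say children will be analysed as independent. The main model is named only as probability modelling; its covariates and error structure are left open, and a full protocol or analysis plan that is not shown may contain a clinician term. That is right. A reader might infer that the plan commits to an independence analysis and that its CIs are bound to be too narrow, but the text supports neither. The undercoverage needs a positive ICC, shared clinicians and an analysis that ignores both.

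Three further inferences also lack support:

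- **A handful of therapists.** No count is given. The figure of "4 child and youth psychiatric units in Region Skåne" says where first visits are screened, not how many clinicians deliver the treatment. Individual, manual-based and supervised delivery may also keep the ICC low.
- **Unclustered controls.** Controls are treated at their home clinics, and some may share a clinician. The article does not say, so a model that makes each control its own cluster could be wrong.
- **Clustering by clinic.** Children are randomised individually. If both arms occur in each clinic, ignoring a common clinic effect does not generally narrow the CI for the arm difference.

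Two things survive. The sample size is a stated figure, and it reproduces without any allowance for clustering. And the treating clinician has to be recorded while treatment is delivered. The background data listed under Measures and Data Collection (gender, age, housing situation, diagnosis) do not include it. That list may be incomplete, but an analysis plan written later could not easily recover the information.

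**Conclusion.** The point holds in conditional form. None of the named analyses accounts for clinician, and the planned power of about 79% has no reserve for clustering. If the clinician ICC is positive, several children share a clinician and the analysis ignores it, the 95% CIs will be too narrow.

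The article cannot settle the size. It runs from nothing of practical importance with about 40 clinicians to a material loss of coverage and power with 8 or fewer at an ICC of 0.05 to 0.10. These figures assume equal caseloads, clustering in the relapse prevention arm only, and a two-sided 5% level. This is an inexpensive improvement that should be made, not a demonstrated error in the main analysis.

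**What to change.** - Record the treating clinician for every child in both arms, starting during delivery.
- In the main model, account for clinician clustering in the relapse prevention arm, either with a partially nested random effect or with cluster-robust standard errors, and apply a small-sample correction in both cases. Extend this to controls if the recorded data show that they also share clinicians.
- Report the number of clinicians, the children per clinician and the estimated ICC.
- State under Sample Size that the planned power assumes no clinician clustering. Once the number of clinicians is known, show the power over a range of ICCs.

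The cost is one extra data field, a few sentences of analysis text and slightly wider CIs. With few clinicians the ICC will be estimated imprecisely, so the method should be fixed in advance and not made to depend on whether the estimated ICC differs from zero.

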### Qualitative Component

In addition to the RCT, the study will be supplemented with a qualitative component with semistructured individual interviews in order to capture participants’ and clinicians’ experiences of the treatment, as well as attitudes about parent-child relationships and parenting needs in carers whose children completed the relapse prevention treatment. Specifically, the interviews with the children will focus on the children’s meaning-making of problem gaming, their experiences of the treatment, as well as their reflections on parent-child relationships before and after treatment. The interviews with the clinicians will focus on the clinicians’ experiences of carrying out the treatment, as well as their understanding of problem gaming. Finally, the interviews with the carers will focus on carers’ attitudes in terms of parent-child relationships before and after treatment of the child, as well as their reflections on potential parenting support needs in terms of their child’s gaming.

All interviews will be conducted by staff with knowledge of qualitative interview methodology. Each interview template will be pilot-tested prior to data collection. The respondents will be offered participation through a physical or digital interview. After the collection phase, the generated data will be analyzed with the help of thematic analysis based on the recommendations by Braun and Clarke [31].

### Dissemination

Findings from the study will be published in peer-reviewed journals and presented at local, national, and international conferences; workshops with key stakeholders; and interviews, pods, seminars, and lectures with general audiences. Results will also be reported to the funders.

The trial was retrospectively registered on ClinicalTrials.gov (NCT05506384; date of registration: April 13, 2022) due to administrative overload.

